# Study protocol for a randomized, controlled trial comparing the efficacy of two educational interventions to improve inhalation techniques in patients with chronic obstructive pulmonary disease (COPD): TIEPOC Study

**DOI:** 10.7573/dic.212261

**Published:** 2014-04-24

**Keywords:** COPD, inhalation techniques, educational intervention, treatment adherence, self-management, patient empowerment

## Abstract

**Background::**

An appropriate inhalation technique and adherence to treatment are both critical determinants of the success of chronic obstructive pulmonary disease (COPD) management. We have observed that up to 75% of patients do not use a successful inhalation technique. Knowledge evaluation and frequent reassessment of inhaler use, together with education of patients and healthcare professionals, can significantly improve the benefits that patients with COPD will derive from inhaler therapy. The objective of this study is to test the efficacy of two educational interventions to improve inhalation techniques in patients with COPD.

**Methods::**

Multicenter randomized controlled trial with 296 patients diagnosed with COPD selected by a non-probabilistic method of sampling from seven Spanish Primary Care Centers. The patients will be divided into three groups by block randomization. The three groups are: 1) control; 2) Intervention A; and 3) Intervention B. The control group will comprise patients with no explanations or written information; the Intervention A group will comprise patients to whom we give written information only; and the Intervention B group will comprise patients to whom we give written information plus instructor training. Every patient in each group will be visited four times during the year of the study at the health centers.

**Discussion::**

Our hypothesis is that the application of educational interventions (A or B) in patients with COPD who use inhaler therapy will increase the number of patients who perform a correct inhalation technique by at least 25%. We will evaluate the effectiveness of these interventions on patient inhalation technique improvement, where feasible within the context of clinical practice.

## Background

Chronic obstructive pulmonary disease (COPD) is a substantial disease burden worldwide [1]. COPD is the fourth most common global cause of death. Its prevalence is expected to increase and is primarily related to tobacco smoking, affecting 5–10% of the adult population [2–4]. It is characterized by airflow limitation or airway obstruction that is only partially reversible, and is usually relentlessly progressive in nature. For patients with COPD, inhalation therapy is the main treatment. Inhalers are the vehicles for the effective administration of medication. They allow high lung deposition of the drug and minimize systemic adverse drug reactions [5]. Patients often do not get the full value of their inhaled medications because they use their inhaler incorrectly. When technique is markedly flawed, suboptimal outcomes typically result [6]. Some of the consequences of poor inhaler technique include reduced therapeutic dosing and disease stability, which can lead to increased morbidity, decreased quality of life, and a high burden on the healthcare system [7].

The fact that patients with COPD are usually older persons means that they generally have more difficulties effecting successful use of inhalers, and this can be related to tremors, coordination, and visual acuity. Increasing age is significantly associated with an increased risk of inhaler misuse, and cognitive deficits may account for some of the increase seen with disease progression [7].

Although safety and efficacy are the primary factors determining the choice of an inhaler device, there is a need to increase knowledge and optimize clinical use of therapeutic aerosols. Since the inhaler technique required for different types of device varies greatly, it seems sensible to prescribe a single type of device for the different drugs required for the patient. However, this is not always possible, and so different drug and delivery device combinations are prescribed; therefore, it is important to ensure the patient can use them [8–10]. In previous studies we demonstrated that over 80% of patients do not perform a correct inhalation technique [11]. A study of 120 patients (60 COPD; 60 asthma) showed that while 98% of the COPD patients said that they knew how to use inhaler devices, only 5 of the 60 COPD patients (8.3%) performed every step correctly [12]. Other studies show a similar percentage of error [13–15]. Further, many inhalers are complicated to use and some require up to eight steps [16].

There is a wide variety of different inhalers; they can be broadly classified into pressurized metered-dose (pMDI), dry powder (DPI), breath-actuated metered-dose (BA-MDI) and soft mist inhalers. Table 1 describes the percentages of mistakes, step by step, seen by Melani A et al. [17,18] and from our own unpublished data. pMDIs are widely prescribed as they are cheap and can deliver a wide variety of medications for asthma or COPD [19]. A previous study demonstrated that only 79% of patients could use a pMDI correctly after expert training [20]. Efficient use of a pMDI requires coordination between simultaneous inhalation and device actuation, a slow and continuous inspiratory flow rate during inhalation, followed by a breath hold of at least 10 seconds. Patients frequently fail to exhale fully before inhalation. Other common errors are high inspiratory flows, not shaking the device before use, and stopping inspiration when the spray reaches the throat [4,9,16]. Sometimes patients put the mouthpiece into their mouths, which prevents them from getting a good inhalation. It has been demonstrated that if patients purse their lips closely around the mouthpiece and inhale, this allows air from around the mouthpiece to enter, increases the airflow, and moves the medication further into the lungs [21]. Other drawbacks of pMDI are that some of them contain environmentally unfriendly propellants and most of them provide no dose counter, so patients do not know the number of doses remaining and may continue to use the device when it is empty [15,22].

There are a number of DPIs currently available. Some of these devices are single dose, and require the loading of a capsule containing the drug in powder form. The main advantage is that there is no need for an aerosol propellant or coordination between actuation of the device and inhalation. In these devices the most common errors are: not placing the device correctly, exhaling into the mouthpiece, low inspiratory flows, and incorrect breath-holding. The most critical mistakes may be exhalation into the mouthpiece and low inspiratory flow, because the humidity and inadequate flow reduce the amount of drug released and its ability to reach the lungs [22,23].

The National Institute for Health and Care Excellence (NICE) and the Global Initiative for Chronic Obstructive Lung Disease (GOLD) guidelines recommend that prior to prescription of a new inhaler for a patient with COPD, the patient should receive training and education in the use of the device. Both guidelines also advise that inhaler technique should be regularly assessed at each clinic visit [24,25]. The quality of the initial instruction is of utmost importance for the outcome of inhalation therapy. Written instructions alone are insufficient in teaching correct inhalation techniques. Verbal instruction and technique assessment and reassessment are essential for patients to achieve a correct technique [26]. The assumption that healthcare professionals can be relied on to provide patient instruction is called into question by several studies, suggesting that the knowledge and skills of those providing instruction are less than optimal. Most studies indicate that only approximately half of healthcare professionals know how to use an inhaler or demonstrate correct technique [7]. To acquire the skills for using the inhaler devices, healthcare professionals and patients must be adequately educated and trained. Bosnic-Anticevich et al. reported that practical demonstration, in addition to verbal and written instruction, is much more effective in improving technique compared with verbal and written instruction alone [27], but this is a small study in patients with asthma and COPD. Further studies must be conducted to reinforce these conclusions.

The aim of the present study is to test the efficacy of two educational interventions (written only and written and verbal instruction) to improve inhalation techniques in patients with COPD.

## Methods

This study has been approved by the Ethical Committees of Primary Care Trust Málaga (December 21, 2010), the Health Area Málaga Este-Axarquía (February 16, 2010) and by the Regional Clinical Assays Committee (January 25, 2011). The protocol follows the guidelines of the Declaration of Helsinki and Good Clinical Practice.

### Participants

A total of 296 patients with COPD, selected by a non-probabilistic consecutive sampling method from seven Spanish Primary Care Centers, will participate in the study. The inclusion criteria will be: confirmed COPD diagnosis in the clinical record (clinical and/or spirometry criteria following SEPAR or GOLD guidelines), belong to the selected Primary Care Centers in the Málaga area, to have been prescribed inhalation therapy (main devices: Handihaler, Turbuhaler, Accuhaler and pMDI), agreement to participate in the study with written informed consent. Exclusion criteria will be: diagnosis of other respiratory conditions which are not included in the COPD definition (bronchiectasis, asthma or cystic fibrosis) and cognitive impairment problems registered in the clinical record (dementia, Alzheimer’s disease, Parkinson’s disease, cognitive decline). All these criteria will be reviewed in the patients’ clinical records.

### Sample size

This has been calculated to detect a difference of 25% in correct inhalation technique between groups (Intervention A or B vs control), with a statistical power of 80% and a confidence level of 95%, assuming a percentage of expected losses of 40%. The final sample size is 296 patients with COPD who meet the inclusion criteria mentioned above.

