### Statistical Analysis

A descriptive statistical analysis will be performed for all the study variables. We will calculate the mean, median and standard deviations for quantitative variables, and the absolute and relative frequency for qualitative variables. The 95% confidence interval will be applied. A baseline comparison will be made between all groups to analyze the comparability using the chi-square test or ANOVA.

The analysis will be made following an intention-to-treat procedure [34].

The between-group comparison for the primary outcome will be explored using the chi-square test (Intervention A vs control; Intervention B vs control; Intervention A vs Intervention B).The Relative Risk Reduction (RRR), the Absolute Risk Reduction (ARR) and the Number Needed to Treat (NNT) will be calculated. Inferences for the secondary outcomes will be made using an analysis of variance (ANOVA) or chi-square test. Each group will be analyzed separately.

Finally, a logistic multivariate regression model will be performed for the primary outcome (performance of correct inhalation technique [yes/no]), considering the intervention as the predictive variable and the rest of the independent measures as the possible modifying factors.

We will use a 5% significance level (*p*=0.05). The SPSS 15.0 and Stata 11.1 statistical packages will be used to run the analysis.

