## Study limitations

One limitation of this study is the selection bias due to the missing data. In order to decrease this bias, we will apply several strategies:
An increase of 40% in the sample size (expected losses)Three phone calls on different days and times for unreachable patientsRescue appointments for the non-attendees to visits (three different appointment dates)In addition we take into account the possible contamination between the control and the intervention groups because of the relationship between subjects in their daily life (neighborhoods, relatives, social networks or associations). However, in another educational intervention study performed with obese patients in our area we did not find a significant level of this effect [35]. We also believe that the intervention characteristics (several steps and individual visits) that we have described will have little influence on contamination between groups.

In order to standardize interventions they will be performed by two professionals trained in communication, the knowledge of disease, and inhalation techniques of the different inhaler devices. Furthermore, we have designed a manual for the researchers where we explain the working plan, the different parts of the intervention, and the protocol in order that they know what they have to measure each time and the details to assess each variable included in the study. In this way, the procedure can be replicated elsewhere.

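### The 80% power describes the patients left after losses, not an all-randomised intention-to-treat comparison, and the larger sample cannot reduce missing-data bias

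*Protocol article*

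**What the plan says.** Three sections of the protocol article bear on this.

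- **Sample size.** The target is a 25-point gap in the share with correct technique, for either intervention against control, "with a statistical power of 80% and a confidence level of 95%, assuming a percentage of expected losses of 40"%. The total reached is 296. No control-group rate is given, and the section does not say whether the 25 points is the effect in patients with an outcome or in everyone randomised.
- **Statistical Analysis.** "The analysis will be made following an intention-to-treat procedure". The primary outcome, correct technique yes or no, is compared pairwise by chi-square at the 5% level. The article gives no rule for a patient without an outcome.
- **Study limitations.** Missing data are named as a source of selection bias. The first measure listed to decrease it is: "An increase of 40% in the sample size (expected losses"). Repeat phone calls and rescue appointments follow.

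Allocation is equal across three arms (Recruitment). Technique is recorded at inclusion and at 3, 6 and 12 months in every arm (Follow-up).

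**The concern.** When a sample size is raised to allow for losses, the target power belongs to the number before the increase, that is, to the patients expected to remain. An intention-to-treat comparison normally refers to everyone randomised. With 40% loss these groups differ greatly, and a chi-square table can treat the lost patients in only two ways. Either it leaves them out, so that two in five randomised patients are excluded under an intention-to-treat label, or it gives each a single yes/no value. If that value carries no intervention effect, the 25-point difference shrinks, and the larger denominator may not make up for it.

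The Study limitations entry adds to the problem. Extra patients improve precision, but if those who stay differ from those who leave, a larger trial estimates the same biased quantity more precisely.

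Two things are at stake: how a null result for either intervention is read, and whether the plan has any analytic protection against a bias that it names itself.

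**Working it through.** **Inputs.** From the article: 25-point difference, 80% power, 5% level (two-sided assumed), 40% losses, 296 patients, 1:1:1 allocation. The control rate is an assumption. I use 25% correct, the complement of the up to 75% incorrect reported in the Discussion. The Background also gives over 80% incorrect (below 20% correct) and 8.3% with every step correct.

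**1. Reproducing 296.** Pooled-variance formula, 25% vs 50%, no continuity correction:

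n = [1.960 × √(2 × 0.375 × 0.625) + 0.842 × √(0.25 × 0.75 + 0.50 × 0.50)]² / 0.25² = 57.7, so 58 per arm.

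3 × 58 / 0.6 = 290, within 3% of 296. Other inputs fit too: 17% vs 42% with continuity correction, divided by 0.6, gives 295-297; 25% vs 50% at a 2.5% level, multiplied by 1.4, gives 294. So 296 does not identify one set of inputs. In each of these routes the 80% belongs to the number before inflation.

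**2. Power in patients left after losses.** 296 × 0.6 / 3 = 59.2 per arm. Exact enumeration of the chi-square test with 59 per arm, 25% vs 50%: 81%. This matches the stated 80%.

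**3. Power if all are analysed and lost patients carry no effect.** 296 / 3 = 98.7, taken as 98 per arm, with 40% lost equally in each arm.

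- Lost = not correct: 0.6 × 25% = 15% vs 0.6 × 50% = 30%.
- Baseline kept: 25% vs 0.6 × 50% + 0.4 × 25% = 40%.

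Both differences are 15 points. Exact power by assumed control rate:

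| Control rate | Observed only, 59 per arm | Lost = not correct, 98 per arm | Baseline kept, 98 per arm |
|---|---|---|---|
| 8.3% | 94% | 92% | 84% |
| 17% | 86% | 80% | 70% |
| 20% | 84% | 77% | 66% |
| 25% | 81% | 72% | 62% |
| 37.5% (not in the article) | 79% | 64% | 57% |

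**4. Other readings the text allows, control rate 25%.**

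- Lost patients keep half the effect: 25 × (0.6 + 0.4 × 0.5) = 20 points, 25% vs 45%, power about 84%.
- The 25 points is already the effect in all 296: about 96%.
- The 40% increase is taken literally as a factor of 1.4: this allows for losses of 1 − 1/1.4 = 28.6%. Power is then about 81% (lost = not correct) or 76% (baseline kept).

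**The case against.** A reader might infer that the trial simply has 62-72% power, or a 28-38% chance of missing a true 25-point effect. The article does not support that. It prescribes no filling rule, and such a rule may sit in a full protocol or analysis plan that is not shown; its absence here is not a fault. Naming missing data as a limitation fits outcomes that stay missing at least as well as outcomes filled in for everyone. If observed patients are analysed in their allocated arm, the 80% stands.

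Zero effect in the lost is also a pessimistic assumption. Intervention patients receive the leaflet or training at inclusion, and loss can be declared after two missed follow-up visits, so a lost patient may have one follow-up result. The control rate is not stated either, and at 8.3% neither rule takes power below 80%. Inflating for losses alongside an intention-to-treat statement is ordinary practice, and 296 itself reproduces.

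All of this stands, and it makes the shortfall conditional. It does not rescue the claim that a larger sample decreases selection bias. Nor does it settle which patients the 80% describes when 40% are expected to be lost.

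**Conclusion.** The point holds in a limited form. The stated 80% corresponds to the patients remaining after losses, while the stated analysis is intention to treat, and the article does not connect the two. Inflation replaces numbers; listing it as a remedy for selection bias is wrong whatever the control rate.

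The cost in power is conditional. It is about 8 to 18 points below the stated 80% (72% or 62%) if the control rate is 25%, 40% are lost equally across arms, and lost patients are counted as failures or held at baseline. There is no shortfall at a control rate of 8.3%, if lost patients keep half the effect, or if only observed patients are analysed. In the last case the 80% is kept by leaving out the lost 40%. This is not an arithmetic error in 296, and the article does not prove the trial underpowered.

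**What to change.** Keep 296 patients and the existing visits.

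1. In Sample size, say that the 80% applies to patients with an observed outcome, and give the control rate used.
2. For the primary all-randomised comparison, use a repeated-measures logistic model or multiple imputation that draws on the baseline, 3- and 6-month technique results already collected. Neither method forces a zero effect on lost patients, and power should stay near 80% if losses are missing at random.
3. Report lost = not correct as a sensitivity analysis, with its conditional power (about 72% at a 25% control rate and 40% loss).
4. In Study limitations, remove the sample-size increase from the measures that decrease selection bias. Phone calls and rescue appointments can stay, since they act on the losses themselves. Say there whether 40% means losses or an increase by a factor of 1.4.

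The cost is a somewhat more complex analysis, feasible in the Stata package already named, that relies on a missing-at-random assumption, and a less favourable conditional power figure in print.

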### Design

Multicenter randomized controlled trial with 1 year of follow-up and four visits (Figure 1). The patients will be divided into three groups by block randomization: control, Intervention A (written information only) and Intervention B (written information and verbal instruction).

### Setting

The study will take place in Primary Care Centers in Malaga, Spain.

### Outcomes

*Primary outcome*: Performance of correct inhalation technique. This will be measured using a template designed following SEPAR (Sociedad Española de Neumología y CirugíaTorácica) guidelines [16] where the interviewer will write down any mistakes. It will be considered a good technique when there are no mistakes registered in the template.

*Secondary outcome:* Participants will be evaluated using inhaler peak flow, functional status (spirometry), mental-cognitive status (mini-mental state examination), dyspnea with the Baseline Dyspnea Index (BDI) [28] and Modified Medical Research Council (MMRC) scale [29]; questionnaires on quality of life (St George’s Respiratory Questionnaire [30], and EuroQoL-5D [31]) and the clinical progress of illness (SeguiEPOC questionnaire) will be recorded.

*Independent* v*ariables:* Independent variables will be: sex, age, educational level, smoking history, comorbidity, COPD severity grade (according to GOLD guidelines [24]), prescribed medication, type and number of devices, family support (Family Apgar Test [32]), and social support (DUKE-UNC Test [33]).

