#### Control group:

Inclusion Visit: all the study data will be recorded and the inhalation technique will be tested.
Visit 1 will take place 3 months after the inclusion visit. Primary and secondary outcomes will be measured (excluding spirometry and quality of life).Visit 2 will take place 6 months after the inclusion visit. Primary and secondary outcomes will be measured (excluding spirometry and quality of life).Visit 3 will take place 12 months after the inclusion visit. All the study data will be recorded.

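### The baseline cognitive score (MMSE) is collected but kept out of the logistic model, because it is listed only as a secondary outcome

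*Protocol article*

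**What the plan says.** All references are to the Protocol article.

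- **Role of the MMSE.** The Outcomes section lists "mental-cognitive status (mini-mental state examination), dyspnea with the Baseline Dyspnea Index (BDI") under the secondary outcomes.
- **Independent variables.** The same section defines these as "Independent variables will be: sex, age, educational level, smoking history, comorbidity, COPD severity grade", followed by "prescribed medication, type and number of devices, family support (Family Apgar Test [32]), and social support (DUKE-UNC Test [33"]). Neither part contains a cognitive measure.
- **Model.** The Statistical Analysis section specifies a logistic regression for the primary outcome, "considering the intervention as the predictive variable and the rest of the independent measures as the possible modifying factors". Secondary outcomes are to be tested by ANOVA or chi-square.
- **Cognition and misuse.** The Background, in a sentence on increasing age and inhaler misuse, adds that "cognitive deficits may account for some of the increase seen with disease progression".
- **Exclusion.** The Participants section excludes "cognitive impairment problems registered in the clinical record (dementia, Alzheimer’s disease, Parkinson’s disease, cognitive decline"). It sets no MMSE threshold.
- **Timing.** All study data are recorded at the inclusion visit and at month 12. At months 3 and 6 the Follow-up section says "Primary and secondary outcomes will be measured (excluding spirometry and quality of life"), so the MMSE is repeated at both.

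**The concern.** The article treats cognition in two ways that do not fit together. In the Background and in the exclusion criteria it precedes poor technique and may contribute to it. In the Outcomes section it is only something to be compared after an inhaler lesson, and no reason is given why a leaflet or a demonstration would change it.

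The placement has a practical effect because the model draws its terms from the list of independent variables. Family and social support can enter as possible modifiers; the only cognitive measure in the trial cannot. This bears on the contrast between the active arms. Intervention A asks patients to read a leaflet and find for themselves where their technique departs from it. Intervention B adds demonstration and repeated practice. Whether the leaflet is enough could well depend on cognitive status, and the model as written cannot address that.

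**Working it through.** **1. Is the MMSE anywhere in the model?** The independent variables are sex, age, education, smoking, comorbidity, COPD severity, medication, devices (type and number), family support and social support: ten entries, none cognitive. The model is the intervention plus these. No other section adds the MMSE.

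**2. Does the exclusion criterion remove the issue?** It acts on what is "cognitive impairment problems registered in the clinical record". Mild or unrecorded impairment can enter the trial, so some variation in MMSE should remain.

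**3. Is a baseline value available?** Yes, since all study data are recorded at the inclusion visit. The Recruitment section places this recording after randomisation and does not say whether the MMSE comes before the leaflet or training. The score is a safe covariate only if it comes first.

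**4. The plan's own figure.** The sample size is 296 for a 25-point difference, 80% power, 95% confidence and 40% losses. The control rate is not given with the calculation. I assume 25% correct, the complement of the 75% incorrect reported in the Discussion, and a two-sided test:

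n = [1.96·√(2·0.375·0.625) + 0.8416·√(0.25·0.75 + 0.50·0.50)]² / 0.25²
= (1.342 + 0.557)² / 0.0625 ≈ 57.7, so 58 per arm.

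58 / (1 − 0.40) = 96.7, so 97 per arm and 3 × 97 = 291 in total, within 2% of 296. A 17% control rate with continuity correction gives 297. The MMSE plays no part in this calculation.

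**5. Patients available to the model.** 296 × 0.60 = 177.6, or about 59 per arm.

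**6. Cost of omitting a prognostic covariate.** This is an illustrative simulation with 2,000 replicates per row: two arms of 59, 25% versus 50% correct, and a standardised baseline covariate. The strength of the covariate is assumed, because the article gives none.

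| Log-odds ratio per SD | Mean unadjusted risk difference | Power, chi-square | Power, adjusted logistic |
|---|---|---|---|
| 0 | 0.255 | 82.1% | 82.1% |
| 0.5 | 0.250 | 81.1% | 81.9% |
| 1.0 | 0.249 | 80.9% | 87.0% |

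The unadjusted difference stays at about 0.25 throughout, so omission does not bias it. The power gain is about 1 point at 0.5, which is no larger than the simulation error of one power estimate (√(0.81 × 0.19 / 2000) ≈ 0.9 points). It is about 6 points at 1.0.

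**7. Degrees of freedom.** MMSE as a linear covariate costs 1. Its interaction with a three-level arm variable costs 2 more, so 3 in all.

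**8. Between-arm MMSE tests.** One three-arm ANOVA at one visit, or at each of three follow-up visits, is 1 to 3 tests. With no effect, the expected number of false positives is 1 × 0.05 = 0.05 to 3 × 0.05 = 0.15.

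**The case against.** The strongest reply is that nothing important changes. Allocation is randomised within centre, the primary comparison is a chi-square test, and the sample size is unaffected. The logistic model is supplementary. It already holds age, education, comorbidity and COPD severity, which carry some of the same information, and recorded dementia and cognitive decline are excluded. Baseline MMSE would still be described and compared between arms. All of this stands, and it limits the point to precision and effect modification. It does not close the gap, because the other variables are only partial proxies for a score the trial already has.

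A second reply is that a condensed article leaves covariate choice to an analysis plan. That is weak here: the article states both the list of independent variables and the rule that fills the model from it.

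A reader might also infer more than the article supports:

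- *That the main result is biased or confounded.* Randomisation prevents this, and step 6 shows an unchanged risk difference.
- *That the article names cognition as a cause of misuse.* The Background says only that deficits may account for some of an increase.
- *That the MMSE will face nine efficacy tests* (3 visits × 3 pairs, 9 × 0.05 = 0.45 expected false positives). Pairwise comparisons are specified only for the primary outcome, and the article does not say that secondary outcomes are tested at every visit.
- *That repeating the MMSE crowds out training time.* The article gives no duration for it, only a visit of 20–30 minutes depending on arm.
- *That adding it is wholly free.* With modification included it costs 3 df in a model that already has about ten variables and about 178 patients.

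**Conclusion.** The point holds in a limited form. As written, the logistic model excludes a measure recorded at the inclusion visit that the article itself links to inhaler misuse and that the record-based exclusion does not fully control. The primary chi-square comparisons and the total of 296 are untouched.

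The definite loss is that the model cannot examine cognition as a modifier of leaflet or training. The loss of precision is conditional: negligible at a log-odds ratio of 0.5 per SD and about 6 points of power at 1.0, under the assumed 25% and 50% rates and 59 patients per arm. The real strength of the association is unknown. The between-arm MMSE tests add little false-positive risk (0.05 to 0.15 expected), but no rationale is given for them. This is a modest flaw, worth correcting because the remedy is nearly free.

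**What to change.** - **Outcomes.** Add the inclusion-visit MMSE score to the independent variables, and state that it is taken before any leaflet or training is given. Use only this value as a covariate, since later scores follow the intervention.
- **Statistical Analysis.** Enter that score in the logistic model as a covariate (1 df). If an MMSE-by-arm interaction is fitted (2 further df), label it exploratory, given about 59 patients per arm after 40% losses.
- **Follow-up MMSE.** Report it descriptively rather than as an efficacy result, or state the reason for testing it between arms. Description keeps the view of cognitive change over the year.

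**Cost.** Wording only: no new data, visits or patients. The small downsides are one to three extra model terms and the loss of one to three between-arm tests.
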